### Sample Size

The total sample and subgroup size were determined by conducting an a priori power analysis using the G-Power software (version 3.1.9.7; G-Power) by applying repeated measures ANOVA and selecting within- and between-group interactions with an effect size *f* set at 0.4 (large effect size), α of .05, and β of .90. Estimation of large effect sizes is based on previous results obtained from among patients with neck pain and on the therapy duration and frequency.

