Stochastic resonance therapy (SRT) is a form of whole-body vibration therapy that uses randomized stimuli that are amplified with the help of noise [27]. The vibration output from SRT is different from that of a regular WBV in that it is random and unpredictable. Thus, the patient is constantly challenged to adapt to the multidimensional perturbations from the device’s standing platform [28,29]. Previous studies have suggested potential therapeutic benefits of the SRT [28,30-32]. For example, Kaut et al [31] reported increased postural stability in patients with Parkinson disease after administration of SRT. SRT is also known to reduce musculoskeletal pains [32,33]. Furthermore, a recent systematic review and meta-analysis indicated improvements in postural control and balance performance in healthy young adults, older adults, and people with lower extremity injuries after stochastic stimulation [34].

Until now, the effects of SRT and WBV in cervical pain are not known. Thus, this study aims to answer the research question which treatment among BLT, WBV, and SRT has the greatest effect in reducing pain intensity, the pressure pain threshold (PPT), and neck disability and in improving CJPS acuity in patients with chronic neck pain.

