### Study Setting and Participants

The study will be conducted at the Reha Center Michaeliskarree GmbH (an outpatient rehabilitation center) in Hof, Bavaria, Germany. Participants will be recruited through advertisement posters placed at the rehabilitation center and other health facilities in the neighborhood. We will recruit a total of 45 participants for the study, who are allocated to 3 arms of 15 participants per group: SRT, WBV, and BLT. We plan to recruit 2 additional patients per group to be sure that our design will not be underpowered in case of an approximately 15% dropout.

The progression of the trial is summarized in Figure 1. Participants will be included in the study if they have grade 1 neck pain without daily interference and grade 2 neck pain, which interferes with daily activities [36] for 3 months or longer, are between the ages of 18 and 65 years, and sign a written informed consent form. The following exclusion criteria are applied: the presence of potential contraindications to vibrations (eg, pregnancy and fresh medical procedures), uncontrolled high blood pressure or low blood pressure, kidney stones, glaucoma, acute thrombosis, advanced osteoporosis, presence of neurological conditions, epilepsy, rheumatoid arthritis, acute hernia, schizophrenia, pacemaker, aneurysm, heart arrhythmias and tumors or metastases, and uncontrolled diabetes. Furthermore, patients with the following pre-existing conditions shall be excluded: vertigo, dizziness, diabetic disorders, vertebrobasilar insufficiency, limiting pain, difficulties understanding instructions, difficulties adopting the required posture on the devices, whiplash-associated disorder, and traumatic injury to the neck.

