### Statistical Analysis

Statistical analyses will be performed using SPSS (version 24; SPSS Inc). Descriptive statistics will be used to report the study population’s demography and characteristics. The Gaussian distribution of data will be assessed using the Shapiro-Wilk test. Thereafter, mixed ANOVA will be used to determine the main and interaction effects of within (before intervention, after intervention 1, after intervention 2, after intervention 3, and follow-up) and between (SRT, WBV, and BLT) factors on the study outcome variables. Mean (SD) values, effect sizes, and 95% CIs are reported.

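### The sample-size paragraph gives β as .90, its stated inputs do not reproduce 45 patients, and its power figure does not cover the between-arm hypotheses

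*Protocol article*

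**What the plan says.** The Sample Size section says that an a priori G-Power calculation for repeated-measures ANOVA determined both the total and the subgroup size. It was run "selecting within- and between-group interactions", with f "set at 0.4 (large effect size), α of .05, and β of .90". The basis given for f is: "Estimation of large effect sizes is based on previous results obtained from among patients with neck pain". The section prints no resulting number of patients.

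The number is in Study Setting and Participants: "We will recruit a total of 45 participants for the study, who are allocated to 3 arms of 15 participants per group".

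The Statistical Analysis section plans a mixed ANOVA with three groups and five occasions ("before intervention, after intervention 1, after intervention 2, after intervention 3, and follow-up").

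The Introduction asks "which treatment among BLT, WBV, and SRT has the greatest effect". Under Expected Findings the authors hypothesise that SRT does better than WBV and that BLT does best of the three.

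**The concern.** Three things in this short paragraph do not fit together.

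1. β is the type II error rate, so β of .90 means 10% power.
2. The named test with the printed inputs, applied to the design the article describes, should lead to 45 patients. Under the usual settings it leads to a much smaller number.
3. The power figure belongs to an omnibus test with (3 − 1)(5 − 1) = 8 numerator degrees of freedom. The research question and the hypotheses concern which arm beats which.

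The third matters most for interpretation. All three arms are active and all are expected to work. A reader who takes 90% as the trial's power to rank the arms could treat a non-significant difference between two of them as evidence that they are alike, when 15 patients per arm could easily have missed a difference of conventional large size.

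**Working it through.** **Inputs from the protocol.** k = 3 groups; m = 5 occasions (Statistical Analysis); f = 0.4 and α = .05 (Sample Size); power .90, reading the printed β as power; N = 45, 15 per arm (Study Setting and Participants).

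**Not given, so assumed.** Correlation ρ between occasions, epsilon ε and the effect-size convention. Base case: ρ = .5, ε = 1, default convention. N is taken in multiples of 3.

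**Step 1: β as printed.** Power = 1 − β = 1 − .90 = .10. In the base case even 6 patients in total give 33% power, so 10% cannot have been the target.

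**Step 2: trying to reproduce 45.** Noncentral F test for the group-by-time interaction:

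λ = f² × N × m × ε / (1 − ρ); df1 = (k − 1)(m − 1)ε; df2 = (N − k)(m − 1)ε.

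Base case, where λ = 0.16 × N × 5 / 0.5 = 1.6N:

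| N total | λ | df | Power |
|---|---|---|---|
| 12 | 19.2 | 8, 36 | .819 |
| 15 | 24.0 | 8, 48 | .923 |
| 45 | 72.0 | 8, 168 | > .999 |

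The smallest N reaching .90 is 15 in total.

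Other settings, with 5 occasions and ε = 1:

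| Setting | Total N for power .90 |
|---|---|
| ρ = 0 | 27 |
| ρ = .3 | 21 |
| ρ = .5 | 15 |
| ρ = .7 | 12 |
| Cohen convention, λ = f²N(m − 1) | 33 |
| SPSS convention, λ = f²(N − k)(m − 1) | 36 |

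N falls as ρ rises, so 27 is the ceiling for non-negative ρ under the default convention.

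**Step 3: which settings give 45.**

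- 2 occasions, ρ = 0, ε = 1: λ = 0.16 × 45 × 2 / 1 = 14.4, df 2 and 42, power .916; 42 patients give .894, so N = 45.
- 5 occasions, SPSS convention, ε = .7: power .915 at 45 and .890 at 42, so N = 45.
- 5 occasions, Cohen convention, ε = .6: power .902 at 45 and .877 at 42, so N = 45.
- 5 occasions, default convention, low ε: values on either side of 45, for example 42 (ε = .5, ρ = 0) and 48 (ε = .25, ρ = .3).

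The article states none of these settings.

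**Step 4: what 15 per arm gives for two arms.** Two-sided two-sample t test at α = .05, unadjusted, df = 28, noncentrality d × √(15/2) = 2.739d. The article gives no pairwise effect, so d is assumed.

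| d (SD units) | Noncentrality | Power |
|---|---|---|
| 0.8 | 2.19 | 56% |
| 1.06 | 2.90 | 80% |
| 1.23 | 3.37 | 90% |

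At d = 0.8, adjusting for baseline raises power to 68% if the baseline correlation is .5 and to 84% if it is .7. A Bonferroni correction for three pairs, without adjustment, lowers it to 38%. With baseline adjustment, 90% power needs d = 1.06 (correlation .5) or 0.88 (correlation .7).

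**The case against.** The strongest reply has four parts.

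**The β entry is a labelling slip that misleads nobody.** It is a slip, and correcting it changes neither design nor analysis. It is still a wrong design figure in a published protocol.

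**An article may leave correlation, epsilon and the effect-size option to the full protocol, and some choices give 45.** This stands. Occasions spaced from minutes to weeks make ε below 1 plausible, and SPSS is the planned analysis software. It therefore cannot be said that the calculation is impossible or that 45 is wrong, and the missing settings are no fault in themselves. What remains is that the printed inputs with ordinary settings lead well away from 45.

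**A reader might infer that a total of 15 was mistaken for 15 per arm.** The coincidence is striking, but nothing in the article shows it. It is a question for the authors to check, not an established error.

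**A reader might also infer that the trial falls short of the power it claims.** The article does not support that. It claims power for the interaction only, and for that test 45 is ample at f = 0.4. It makes no pairwise claim, and applying the interaction f of 0.4 to a comparison of arms at one time point would mix two different parameters. The article also plans effect sizes with 95% CIs and nowhere says that a non-significant difference would mean equal effectiveness. The remaining point is narrower: the stated hypotheses are pairwise, and the power figure says nothing about them.

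**Conclusion.** The concern holds in a limited form.

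- **β of .90 is wrong as written.** This needs no assumption.
- **45 is not reproducible from the stated inputs.** The standard settings give 15 in total, and the sphericity settings tried give at most 36. This rests on 5 occasions, as in the planned analysis, and on reading β as power. Settings that reach 45 exist but are unstated.
- **The stated interaction is not underpowered.** At 45 its power exceeds 99.9% for f = 0.4, ρ = .5 and ε = 1.
- **That power does not extend to the between-arm hypotheses.** With 15 per arm and no adjustment, power for one pair is about 56% at d = 0.8; 80% needs d = 1.06 and 90% needs d = 1.23. These figures depend on an assumed d, and baseline adjustment would improve them.

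**What to change.** Rewrite the Sample Size paragraph:

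1. Replace the β entry with power .90 (β = .10).
2. State the inputs actually entered (groups, occasions, correlation, epsilon, effect-size option) and the N they returned, and reconcile that N with 45. In doing so, check whether a total was carried over as a per-arm figure.
3. Say that the power figure applies to the omnibus group-by-time interaction only.
4. Add what 15 per arm can detect between two arms: 80% power at d = 1.06 and 90% at d = 1.23, unadjusted. If a baseline-adjusted figure is given, state the correlation assumed.
5. State that non-significant differences between arms will be interpreted from their confidence intervals and not read as equivalence.

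The cost is wording only. No extra patients and no change of design are needed. The downside for the authors is a less favourable power statement for the pairwise comparisons.

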### Statistical Analysis

Statistical analyses will be performed using SPSS (version 24; SPSS Inc). Descriptive statistics will be used to report the study population’s demography and characteristics. The Gaussian distribution of data will be assessed using the Shapiro-Wilk test. Thereafter, mixed ANOVA will be used to determine the main and interaction effects of within (before intervention, after intervention 1, after intervention 2, after intervention 3, and follow-up) and between (SRT, WBV, and BLT) factors on the study outcome variables. Mean (SD) values, effect sizes, and 95% CIs are reported.

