### Outcome Measures

#### Overview

Pre- and postintervention measurements and outcome data shall be assessed by [name]. [name] is a sport scientist with a cumulative work experience of 6 years as a physical education teacher and sports therapist. [name] is trained in using the underlisted assessment instruments and procedures.

Pain intensity, PPT, neck disability, and CJPS are measured before, immediately after, and 15 minutes after the first intervention session and after 4 weeks of the intervention. A follow-up postintervention measurement will be taken after 4 weeks.

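### The five-occasion mixed ANOVA keeps only patients with complete data, so anyone lost after the first session is dropped from the comparison along with the measurements already collected

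*Protocol article*

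**What the plan says.** Under Statistical Analysis the protocol article fixes software and method: "Statistical analyses will be performed using SPSS (version 24; SPSS Inc", and then "mixed ANOVA will be used to determine the main and interaction effects of within" and between factors. The within factor has five levels: "before intervention, after intervention 1, after intervention 2, after intervention 3, and follow-up". The between factor is the three arms.

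The Overview under Outcome Measures gives the timing: "before, immediately after, and 15 minutes after the first intervention session and after 4 weeks of the intervention", followed by "A follow-up postintervention measurement will be taken after 4 weeks". Three of the five occasions therefore surround the first training session, the fourth comes at the end of the 4-week programme, and the fifth is the follow-up.

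Study Setting and Participants gives the numbers: "We will recruit a total of 45 participants for the study, who are allocated to 3 arms of 15 participants per group". Two further patients per group are planned so that "our design will not be underpowered in case of an approximately 15% dropout". The article mentions no other measure against loss of patients.

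**The concern.** A mixed (split-plot) ANOVA treats the five occasions as one row per patient, and its standard form needs the row to be complete. A patient without the week-4 or the follow-up value leaves every within, between and interaction test for that outcome. The timing makes this costly, because loss can hardly occur before the third measurement.

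The result would be a comparison of completers. The research question is which of three treatments works best. The arms differ in how demanding they are, pain and disability are self-reported, and the Limitations section says that the data assessor could not be blinded. If patients who respond poorly or tolerate the training badly leave more often in one arm, the completers in that arm give too favourable a picture. Recruiting extra patients replaces numbers. It does not restore the randomised groups.

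**Working it through.** **Inputs from the article.** Three arms of 15 (45 in total); 2 extra per arm; allowance of about 15% dropout; five occasions, three of them in the first session; f = 0.4, α = .05, and a stated β of .90, read here as power 0.90.

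**Assumed.** Compound symmetry with correlation ρ between 0.3 and 0.7, since the article gives none.

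1. *The article's own numbers.* 45 + 3 × 2 = 51 randomised. Exact inflation would be 45/0.85 = 52.9, so 53; 51 is close to that. With 15% lost, 51 × 0.85 = 43.35, so about 43 complete patients. With 5% or 25% lost, 51 × 0.95 = 48 and 51 × 0.75 = 38.

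2. *Data discarded.* 51 × 5 = 255 planned measurements per outcome. 51 × 0.15 = 7.65, so about 8 patients are lost. Each already has 3 or 4 values: 8 × 3 = 24 to 8 × 4 = 32 collected measurements unused.

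3. *Week-4 precision, loss only at follow-up.* A mixed model estimates the change from baseline to week 4 from all n patients, whereas complete cases use 0.85n. Variance ratio = 1/0.85 = 1.18, and standard error ratio √1.18 = 1.085.

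4. *Precision otherwise.* Suppose a lost patient has p earlier values. The residual variance of the missing value given those p values, in units of σ², is r = 1 − pρ²/(1 + (p − 1)ρ). The variance of a change is 2(1 − ρ). With w = r/[2(1 − ρ)], complete-case variance over mixed-model variance is (1/0.85)/(1 − w + w/0.85).
   - Lost before week 4 (p = 3), ρ = 0.5: r = 1 − 0.75/2 = 0.625 and w = 0.625; ratio = 1.1765/(0.375 + 0.7353) = 1.06. For ρ = 0.3 and 0.7 the ratios are 1.065 and 1.056.
   - Follow-up contrast, lost only at follow-up (p = 4), ρ = 0.5: r = w = 0.6; ratio = 1.1765/(0.4 + 0.7059) = 1.064. For ρ = 0.3 and 0.7 the ratios are 1.067 and 1.062.
   - A variance ratio of 1.06 is a standard error ratio of √1.06 = 1.03.

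5. *Power.* The 45 does not follow uniquely from the stated inputs, because the correlation and the number of measurements used are not given. With λ = f²Nm/(1 − ρ), df1 = 2(m − 1) and df2 = (N − 3)(m − 1), one setting that returns exactly 45 is m = 2, ρ = 0. Power there is 0.894 at 42 patients, 0.916 at 45 and 0.948 at 51. About 43 completers therefore still give close to 0.90.

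6. *How far a mixed model helps if loss depends on the unseen value.* Suppose one arm loses the worst 15% on the last occasion. The complete-case mean for that occasion shifts by φ(z)/(1 − q) = 0.27 SD. Simulation under the assumed correlations gives a remaining shift of 0.13 to 0.24 SD with an unstructured mixed model. At 30% the figures are 0.50 against 0.27 to 0.45 SD. At week 4 the complete-case shift in the 15% scenario is ρ × 0.274, or 0.08 to 0.19 SD. The mixed model avoids that shift, because everyone's week-4 value is used.

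**The case against.** The strongest reply is that the article states no deletion rule, analysis set or imputation method, that an article may leave these to a fuller document, and that the extra recruitment already answers dropout. Part of this stands. Deletion is inferred from the named method and is not written down. The extra patients do largely cover the loss of power. The software is not at fault either, since SPSS also fits mixed models. But the point is directed at a method that the article names, and nothing in the article provides for imputation.

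Several stronger readings are tempting and are not supported:
- A reader might infer that 15% dropout is expected. The text presents it as a contingency.
- A reader might take 0.27 or 0.50 SD as the bias to be removed. These are worst cases for one arm, with loss driven by the unobserved outcome. Similar loss in every arm would largely cancel, and a mixed model removes only part of the last-occasion shift.
- A reader might set such shifts against a distance between arms derived from f = 0.4. Under Sample Size, f is set for the interaction of time and group, so it does not translate into a one-way distance between arm means.
- A reader might quote an 8.5% rise in standard error throughout. Against a mixed model this holds only at week 4 with loss confined to follow-up. Elsewhere it is about 3%.

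**Conclusion.** The concern holds as a recommendation about the choice of analysis. Followed as written, the plan gives a completers-only comparison and discards measurements already taken: about 43 of 51 patients analysed and some 24 to 32 values per outcome unused, if loss reaches the 15% allowed for. The cost in precision is small: a variance ratio of about 1.06, rising to 1.18 for week 4 when only the follow-up is missed. These ratios rest on compound symmetry with correlations of 0.3 to 0.7.

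The main reasons to change are possible bias from unequal loss between arms and the waste of data. Neither the direction nor the size of any bias can be predicted from the article.

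**What to change.** State as primary analysis, for each outcome, a linear mixed model (SPSS MIXED, REML) of all randomised patients in their allocated arm, using every available measurement, with terms for arm, occasion and arm by occasion. Keep the complete-case mixed ANOVA as a sensitivity analysis. State that the model is valid under missing at random and would only partly reduce bias if loss depends on the unobserved outcome.

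The cost is a change of wording; data and software stay the same. The downside is more covariance parameters in a small sample: an unstructured matrix over five occasions has 5 × 6/2 = 15. The plan should therefore name in advance a simpler covariance structure to use if the unstructured one does not converge. The article says that analysis starts only once all participants have finished, so at the time of publication the change could still be made before analysis began.

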## Discussion

### Expected Findings

We hypothesize that all 3 interventions will reduce neck pain and improve the sensorimotor function of the cervical spine. Furthermore, we hypothesize that SRT elicits larger effects than WBV owing to the random and multidimensional nature of the former, thus being a more challenging application of the vibration stimuli. Finally, we hypothesize that BLT elicits the most beneficial effects as it incorporates the coordinatively most challenging tasks and is known to upregulate the inhibitory GABAergic system in the brain, which is also needed to suppress the perception of pain.

Manufacturers of vibration devices have touted their benefits for muscle activation, bone strengthening, and treatment of several health conditions. Indeed, some of these claims are supported by research, as suggested by the latest up-to-date reviews of the literature and meta-analysis [43,44]. However, to the best of our knowledge, this would be the first study to investigate the treatment effects of SRT and WBV in patients with chronic nonspecific neck pain and to compare these effects with BLT. The results from this study will contribute to our understanding of the role of WBV (stochastic and nonstochastic) and BLT in the management of chronic neck pain. It is hoped that this study spurs further research in the application of SRT, WBV, and BLT as treatment options for neck pain. Future studies should further explore how the human neck region responds to WBV stimuli and if this response is correlated with pain reduction and sensorimotor function improvement.

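### The question is which of three arms is best after training, but the only tests fixed are omnibus mixed-ANOVA effects over five occasions; baseline-adjusted arm contrasts at the end of the programme should be primary

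*Protocol article*

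**What the plan says.** The objective is comparative. The Introduction asks "which treatment among BLT, WBV, and SRT has the greatest effect in reducing pain intensity, the pressure pain threshold (PPT), and neck disability". Joint position sense is the fourth outcome in that question. Under Expected Findings the authors add an order: "we hypothesize that SRT elicits larger effects than WBV", and "we hypothesize that BLT elicits the most beneficial effects".

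The Statistical Analysis section fixes the test: "mixed ANOVA will be used to determine the main and interaction effects of within (before intervention, after intervention 1, after intervention 2", continuing to the fourth measurement and follow-up. The within factor has five levels, "before intervention, after intervention 1, after intervention 2, after intervention 3, and follow-up", so the pre-treatment score is one level of the outcome. The other factor is "between (SRT, WBV, and BLT) factors on the study outcome variables". Means, effect sizes and 95% CIs are promised, without saying of which comparison.

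The Outcome Measures overview puts four outcomes on an equal footing: "Pain intensity, PPT, neck disability, and CJPS are measured before, immediately after, and 15 minutes after the first intervention session and after 4 weeks". Two of the four post-baseline occasions therefore fall within minutes of the first session. No primary outcome, decisive time point or between-arm contrast is named. The Sample Size section powers the within-between interaction, with f = 0.4 and α = .05; the β of .90 is read here as 90% power.

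**The concern.** The question concerns the order of three arms after four weeks of training. The fixed tests concern something else.

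- The interaction asks whether the three five-point profiles are parallel. Rejection says that they differ somewhere, not which arm is better or when.
- The group main effect does compare arms, but on the average of five scores, of which one cannot carry a treatment effect and two reflect a single session.

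With four outcomes and no decisive contrast, a claim that one arm has the greatest effect could rest on an interaction driven by a short-lived response on any of them.

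**Working it through.** **Inputs.** From the article: 3 arms, 5 occasions, 15 per arm (45 in total), f = 0.4, α = .05, 4 outcomes. Assumed, because the article gives none: correlation .5 between any two occasions (compound symmetry), outcome SD 1, and the effect patterns below. Simulated figures come from 3,000 to 4,000 trials per case.

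**1. The plan's own figure.** For the interaction, λ = f²·N·m·ε/(1−ρ), with df (k−1)(m−1)ε and (N−k)(m−1)ε. With k = 3, m = 5 and ε = 1, 90% power needs N = 27, 21, 15 or 12 for ρ = 0, 0.3, 0.5 or 0.7. N = 45 appears only under settings not stated, such as m = 2 and ρ = 0: λ = 0.16 × 45 × 2 = 14.4 on 2 and 42 df, power 91.6%. So 45 can be neither confirmed nor called wrong, and the point does not depend on it. Whatever the settings, the power belongs to the interaction.

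**2. A same-day effect only.** One arm is 0.8 SD better at the two occasions after session 1 and equal at week 4 and follow-up.
- Sum of squares of arm deviations: 0.533² + 2 × 0.267² = 0.427. Of the occasion pattern (0, 1, 1, 0, 0): 2 − 4/5 = 1.2.
- λ = 15 × 0.427 × 1.2 / 0.5 = 15.4 on 8 and 168 df, giving power of about 79%.
- Simulation: interaction significant in about 77-79% of trials; a baseline-adjusted comparison at week 4 rejects in about 5%, its nominal rate.

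**3. The group main effect.** Effects of −0.49, 0 and +0.49 SD at week 4 and follow-up only.
- Averaged over five occasions, each shrinks to 2/5: 0.49 × 0.4 = 0.196 SD.
- Variance of a five-occasion mean: (1 + 4 × 0.5)/5 = 0.6.
- λ = 15 × 2 × 0.196² / 0.6 = 1.92 on 2 and 42 df, power about 20%. Simulation: 18-21%.

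**4. The contrast that answers the question.** Same effects, best versus worst at week 4, difference 0.98 SD.
- Baseline-adjusted: SE = √(0.75 × 2/15) = 0.316, ratio 3.10, power about 85% at .05. Simulation: 82-85%.
- On change scores: SE = √(1 × 2/15) = 0.365, ratio 2.68, power about 75%. Simulation: 72-75%. Baseline adjustment thus gains about 10 points.
- Baseline-adjusted under Holm over three pairs: 69-72% in simulation.
- Greenhouse-Geisser-corrected interaction in the same scenario: roughly 70-84%, depending on the correlation pattern.
- Best arm shown better than both others under Holm: about 20-22%. The neighbouring contrasts are only 0.49 SD (ratio 0.49/0.316 = 1.55).

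**5. Four outcomes.** If independent, four interaction tests at .05 give 1 − 0.95⁴ = 18.5% chance of at least one false positive. This is an upper-end figure, because the outcomes come from the same patients and are related.

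**The case against.** The strongest reply is that a group-by-time interaction is a standard way to test differential change, that it is the effect the plan powers, and that follow-up comparisons, sphericity corrections and multiplicity rules usually sit in an analysis plan that is not shown. Much of this stands, and it rules out several stronger readings.

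- *That baseline as a level makes the ANOVA invalid.* It does not. Under the null with compound symmetry the interaction rejects in 4.7-4.8% of simulated trials.
- *That the interaction will be run uncorrected and so be too liberal.* The article does not say this. Any inflated error rate would need both an assumed uneven correlation and an assumed omission.
- *That every F-test on every outcome is a route to a superiority claim.* Time main effects compare no arms; they serve the separate hypothesis that all three treatments help. Only between-arm tests count here.
- *That the planned ANOVA loses power overall.* Only the group main effect clearly does. If one arm is 0.8 SD better at both week 4 and follow-up, the interaction reaches 78.7% against 70.2% for a single week-4 baseline-adjusted comparison.
- *That the trial could never name a best arm.* Pairwise follow-up tests in an unseen plan could do so.

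The mismatch remains. The article does not merely omit detail: it states which effects will be tested, and they do not match its question. Pairwise tests chosen after a significant interaction, over four outcomes and several occasions, would leave the choice of decisive comparison open.

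**Conclusion.** The point holds as a mismatch between objective and fixed analysis, not as a claim that the ANOVA is invalid. The interaction can be significant in about 77-79% of trials when the arms do not differ at week 4, and the group main effect has about 20% power when effects appear only at week 4 and follow-up. Baseline-adjusted contrasts at the end of the programme address the stated question and gain about 10 points of power over change scores.

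The sizes rest on 15 analysed per arm, correlation .5 and the assumed effect patterns; other values would move them. The logic, that an 8-df test over profiles does not order three arms at one time, rests on none of these.

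**What to change.** Before analysis starts, amend the Statistical Analysis section to:

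- model post-baseline scores with arm, occasion, arm-by-occasion and the baseline value of that outcome as covariate (for example, a linear mixed model with unstructured covariance);
- name one primary outcome, chosen by the sponsor (pain NRS is an example), at the end of the 4-week programme;
- make the contrasts BLT−SRT, BLT−WBV and SRT−WBV at that time the primary analysis, with Holm adjustment and 95% CIs;
- report the two same-day occasions as a separate acute-effect analysis and the other outcomes as secondary;
- not use the group main effect as evidence of superiority.

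This costs a paragraph and an amendment, with no new data; the article says that analysis begins only after all participants finish.

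The downside should be stated openly. In the scenario above, Holm lowers best-versus-worst power from about 82-85% to about 69-72%, similar to or below the corrected interaction, and the best arm beats both others in only about one trial in five. The stated 90% power should stay attached to the interaction, and the sample size should be re-justified for the contrasts. As a guide, with baseline correlation .5 (assumed), 90% power for a 0.8 SD pairwise difference needs 26 per arm at α = .05, or 33 at .0167. If recruitment cannot change, the report should say that ranking the arms is likely to remain inconclusive unless differences are large.
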